***c. Study procedures - treatment***

*Randomization arm A: lumpectomy with sentinel lymph node procedure, followed by radiotherapy of the*

*breast*

Patients randomized for control arm A will be treated with lumpectomy and the SLN procedure, followed by radiotherapy of the breast. In case a (non-)SLN metastasis is detected, completion axillary treatment is performed if indicated by the Dutch breast cancer guideline; i.e. either no completion axillary treatment, or completion axillary lymph node dissection, or radiation therapy of the axilla +/- periclavicular lymph nodes. During follow-up the axilla will be assessed by physical examination. In case of the suspicion of an axillary lymph node metastasis with physical examination, an axillary ultrasound (+/- tissue sampling) is indicated. When a metastasis is cyto- or histopathologically confirmed, accurate staging for distant metastases is performed according to the Dutch breast cancer guideline. A delayed ALND is performed if indicated by the multidisciplinary team.

*Randomization arm B: lumpectomy without further axillary staging, followed by radiotherapy of the breast*

Patients randomized for study arm B will be treated with lumpectomy followed by radiotherapy of the breast. These patients will not undergo the SLN procedure. During follow-up the axilla will be accurately assessed by physical examination. In case of the suspicion of an axillary lymph node metastasis at physical examination, an axillary ultrasound (+/- tissue sampling) is indicated. When metastasis is cyto- or histopathologically confirmed, accurate staging for distant metastases is performed. A delayed ALND is performed if indicated by the multidisciplinary team.

*Sentinel lymph node procedure*

The SLN procedures will be performed using technetium-99m Nanocolloid as a radioactive tracer and blue dye / patent blue for lymphatic mapping. Both are injected into breast parenchymal tissue surrounding the tumour, biopsy cavity or periareolar. The tracer will search its way through draining lymph vessels to the first receiving lymph node. This SLN will be identified and harvested by use of the following triple technique: lymphoscintigraphy, intraoperative use of the gamma probe, and intraoperative detection of the blue lymphatic vessels. Palpation of the axilla through the incision after removal of tracer-labelled SLN’s should be performed to identify and remove suspicious (non-SLN) nodes.

⮚ *Pathological assessment - the sentinel node*

As a minimal requirement three histological levels (500 micron distance) for each SLN are examined.

On each level two parallel sections are performed, one for immunohistochemistry and one for haematoxylin and eosin (H&E) staining. Immunohistochemical (IHC) staining is performed for markers containing at least cytokeratin 8 and 18 (e.g. CAM 5.2, NCL5D3). Cytokeratin IHC staining is performed only when H&E staining is negative. Lymph nodes submitted for pathological examination which are marked by the surgeon as non-sentinel nodes are examined with H&E and if negative with cytokeratin IHC staining.

The exact diameter of every SLN must be determined, as well as describing the occurrence of extranodal growth. Isolated tumour cells (<0.2mm) are considered as SLN negative.

*Local treatment primary tumour - breast conserving therapy*

Breast conserving therapy is defined as lumpectomy followed by whole breast irradiation, according to the Dutch breast cancer guideline. Patients are amenable to undergo breast conserving therapy when a good cosmetic result and an equally good locoregional control can be expected according to physical and radiological findings.

As described in the Dutch breast cancer guideline, re-excision is required if invasive tumour or ductal carcinoma in situ reaches into a large area (>4mm) or multiple small areas in the inked resection margin (non-radical). In case a mastectomy is performed as re-excision, the SLN procedure should be performed at time of the mastectomy for patients initially treated according to arm B. Re-excision is not required if the tumour reaches into a limited area (≤4 mm) in the inked resection margin (focal non- radical). Local control can be achieved by adjusting radiotherapy fields and dose.

To facilitate accurate tumour bed localization for irradiation, MRI-compatible clips are positioned intraoperative around the tumour bed after the lumpectomy, as followed: in the medial, lateral, superior and inferior edge of the tumour bed (between skin and fascia, at the level of the tumour) and one clip is placed posterior on the deepest point (usually the pectoral fascia). Radiation therapy is given according to the guidelines described below.

*Radiation therapy details*

*Dose and fractionation*

A fractionation scheme equivalent to 25 x 2 Gy, 5 fractions per week must be applied. Most Dutch centres use a scheme of 15 x 2.67 Gy or 16 x 2.66 Gy, 5 fractions per week. Possible indications for a boost (dose equivalent to 8 x 2 Gy) to the rim of tissue of 1.5 cm around the primary tumour are: patients 50 years or younger, grade 3, or vascular invasion. In case of focal irradical resection, a higher boost dose to an equivalent to 10-13 x 2 Gy can be considered. A simultaneous integrated boost is recommended, with the high fraction size not exceeding 2.67 Gy.

Partial breast irradiation is not allowed. In case a participating centre is also involved in a study concerning partial breast irradiation, we suggest the following: eligible patients aged ≥49 years will be informed about participation in the trial concerning partial breast irradiation, and eligible patients aged <49 years will be informed about participation in the BOOG 2013-08 trial.

*Delineation*

Delineation or target volumes and organs at risk should be performed using the European Society for Radiotherapy & Oncolology (ESTRO) guidelines of v. Offeresen et al. [58].

Delineation of the tumour bed, including a clinical target volume (CTV) and a planning target volume (PTV) is obligatory, irrespective whether a boost is applied or not. In addition, delineation of the axillary nodal regions, axilla level 1, 2, Rotter and 3 is obligatory, even when there is no indication for axillary radiation. Delineation of the supraclavicular nodes is only required if part of the target volume. Delineation of breast tissue is optional.

In case of left-sided breast cancer, delineation of the heart and lungs is obligatory; delineation of the other normal structures is optional.

*Technique/ dose distribution*

The dose in the target volume (breast +/- axilla +/- periclavicular nodes) must be between 95%-107% of the prescribed dose. The Central Lung Distance (CLD) must be < 3 cm (in case of tangential fields) and/or the mean lung dose < 7.5 Gy; the Maximum Heart Distance (in case of tangential fields) must be < 1 cm, and the heart volume receiving > 10 Gy should be < 15%. If lung or heart constraints cannot be met, some underdose in the breast can be accepted to reach the constraints, provided that the PTV of the tumour bed is adequately covered. Breath holding techniques to reduce heart dose in left sided breast cancer are highly recommended.

For evaluation purposes: the minimum, maximum and mean dose of the axilla level 1, 2, Rotter, and 3 should always be recorded.

*Pathological assessment - the primary tumour*

The pathological size and surgical margin (tumour-free margin) of the primary tumour must be assessed. The hormone receptor status must be determined by immunohistochemical staining and is considered positive if ≥10% of the cells stain positive. HER2-status is determined by immunohistochemistry and in case of 2+, by CISH or FISH. Histological tumour grading will be assessed according to the Bloom- Richardson grading system. The histological tumour type must be defined according to the World Health Organization. Presence of lymphovascular invasion is defined as one or more tumour cells in a lymphatic or vascular structure.

⮚ *Modified Bloom-Richardson grading system*

The grading system consists of three components of the tumour morphology: the extent of tubule

formation, the nuclear polymorphism and mitotic activity defined as the number of mitoses per 2 mm^2^. A score of 1, 2 of 3 is assigned to each of these components. The histological grade is determined by the sum of these scores.

Level of tubule formation: 1 = > 75%

2 = 10-75%

3 = < 10%

Nuclear polymorphism: 1 = comparable to normal epithelium

2 = enlarged, vesicular, small nucleoli

3 = polymorphic, vesicular, large nucleoli

Mitotic activity: 1 = 0 through to 7 mitoses per 2 mm^2^

2 = 8 through 12 mitoses per 2 mm^2^

3 = 13 or more mitoses per 2 mm^2^

The histological grade is I for the scores 3-5, II for 6-7, and III for 8-9.

*Primary or adjuvant systemic therapy*

The administration of systemic therapy is not mandatory in this trial. The indication for adjuvant systemic therapy is determined according to the current Dutch breast cancer guideline and multidisciplinary approach. Adjuvant! Online can also be used to estimate the 10-years breast cancer specific survival and the risk reduction by systemic therapy, with or without knowledge of the pathological nodal status. Validated gene expression profiling can be used as an addition to clinicopathologic characteristics, in case of doubt about the indication for adjuvant systemic therapy based on the traditional prognostic factors.

Primary systemic therapy is allowed, but study patients must have a clinical T1-2 status amenable to breast conserving surgery pre-systemic therapy. In patients in study arm B in whom breast conserving surgery is no longer feasible after primary systemic therapy, the SLN procedure will be performed afterwards.

***d. Study procedures - follow-up***

After inclusion a follow-up period of 10 years follows:

Year 1 - 5: physical examination of the axilla and a mammography once yearly

Year 6 - 10: physical examination of the axilla once yearly

≤ 60 years: mammography once yearly

> 60 years: mammography once every two years

Additional imaging techniques for detecting possible recurrence/metastasis will only be performed on indication.

⮚ An axillary ultrasound is performed in patients with a clinical suspicion (physical examination)
of axillary lymph node metastases during follow-up. If an axillary lymph node metastasis is
confirmed (cyto-/histology), staging for distant metastatic disease is mostly performed according
to the Dutch breast cancer guideline.

⮚ Staging for metastatic disease is mostly performed (according to the Dutch breast cancer
guideline) in patients with a clinical suspicion of distant metastatic disease during follow-up.
Physical examination of the axilla must then always be performed for the detection of possible
axillary lymph node metastases. An axillary ultrasound is only performed in patients with a
clinical suspicion (physical examination) of axillary lymph node metastases.

**Table 1. Timeline BOOG 20913-08 study**

|  |  |  | **Year** | | | | | | | | | |
| --- | --- | --- | --- | --- | --- | --- | --- | --- | --- | --- | --- | --- |
| **Required Investigations** | **Prestudy** | **0.5** | **1** | **2** | **3** | **4** | **5** | **6** | **7** | **8** | **9** | **10** |
| Mammography | X |  | Once yearly | | | | | ≤ 60 years: once yearly  ≥ 60 years: once in two years | | | | |
| FNA-core biopsy ¨rimairy tumour | X |  |  |  |  |  |  |  |  |  |  |  |
| Receptor status (ER, PR, HER2, if known) | X |  |  |  |  |  |  |  |  |  |  |  |
| Physical examination axilla | X | Once yearly – outpatient clinic | | | | | | | | | | |
| Axillary ultrasound | X | On indication | | | | | | | | | | |
| Staging for distant metastatic disease |  | On indication | | | | | | | | | | |
| QoL questionnaires* | X | X | X | X | X |  | X |  |  |  |  | X |
| Questionnaire Health care utilization and costs patients* | X | X | X | X | X |  |  |  |  |  |  |  |

* = until a total of 1056 patients is reached

***e. Study procedures - axillary morbidity rate and quality of life***

**Introduction**

Omitting the SLN procedure in clinically node negative breast cancer patients undergoing breast conserving therapy might positively influence the axillary morbidity rate and quality of life. Although the SLN procedure is less invasive compared to an axillary lymph node dissection, complications do not rarely occur; most reported are seroma, hematoma, anaphylactic reaction, lymphoedema, numbness, tingling and pain [12-14]. Severe lymphoedema occurs in still 8% of patients undergoing only this axillary procedure after a follow-up of only 3 years [16]. These findings however are influenced by other therapies, such as the breast surgery itself, breast irradiation or adjuvant systemic therapy. Patients in this study are randomized to undergo either the SLN procedure (either with or without completion axillary treatment) or no SLN procedure. All patients will undergo the same breast treatment (lumpectomy followed by radiation of the breast). The SLN procedure is omitted in the experimental study group. Our study will therefore be the first to provide precise information on the influence of the SLN procedure on the axillary morbidity rate and quality of life.

Further, not performing the sentinel lymph node procedure and thereby possibly leaving supposed tumour load behind, could negatively influence patient’s well-being, with more insecurity and anxiety towards their future. Though, a study showed that trait anxiety rather than the diagnosis breast cancer determined whether patients experienced a low quality of life [59].

**Patient selection**

All patients eligible for the study will be asked to complete the questionnaires once pre-operative and on regular basis post-operative, as shown in the timeline, until a total of 1056 patients eligible for evaluation is reached, equally divided over both treatment arms. Patients are eligible for evaluation only when at least two following questionnaires are completed, of which a completed preoperative questionnaire is mandatory. No patient selection will be performed in order to accomplish a representative study population in accordance to the general breast cancer population.

**Organisation**

The surgeons of the participating centers are responsible for inclusion of patients and handing out the first (preoperative) questionnaire. IKNL Clinical Trial Centre is responsible for the transmission of the questionnaires during follow-up to all included patients. Addresses are collected on the informed consent form, on which patients sign the informed consent, as well as if they do or do not agree that their address can be collected from their general practitioner after 10 years of follow-up, in order to prevent lost to follow-up due to migration. Patients can return the completed questionnaires in self-addressed envelopes to study coordinator [name], Maastricht University Medical Centre+.

**Methods**

To assess the Quality of Life of breast cancer patients in this study, we will use the Dutch version of two validated Quality of Life questionnaires of the EORTC, QLQ-C30 and QLQ-BR 23 (developed specifically for the use in breast cancer patients) and the Dutch version of the EQ-5D-5L [60, 61]. To assess the subjective morbidity we will use the validated “Lymph oedema Functioning, Disability and Health” (Lymph-ICF) questionnaire, which assesses the impairments in function, activity limitations and participation restrictions of patients with arm lymph oedema [62]. A validated short Dutch version of the Spielberger State-Trait Anxiety Inventory (STAI-trait) and the NEO Five Factor Inventory (NEO-FFI) is used to measure if anxiety and personality traits influence the outcome of Quality of Life [63]. These questionnaires are provided pre-randomization and sequentially post-randomization at 6 months 1, 2, 3, 5 and 10 years. The questionnaires will be sent out to up and including patient 1056.

**Informed consent for quality of life**

All patients included in QoL study will be informed about the aims and procedure of the study. They will be informed about the strict confidentiality of their patient data. Axillary morbidity and quality of life assessment is part of the study procedures, therefore written informed consent is obtained simultaneously with the informed consent of the other study procedures, as described previously. The informed consent form is part of the documents to be submitted to the METC for approval. It is the responsibility of the METC to guarantee that this form is conform ICH-GCP guidelines.

It will be emphasized that the participation is voluntary and that the patient is allowed to refuse further participation in the protocol whenever she wants. This will not prejudice the patient’s subsequent care. Documented informed consent must be obtained for all patients included in the study before they are randomized in the study. The written informed consent form should be signed and personally dated by the patient.

***f. Cost-effectiveness analysis***

**Introduction**

In order to identify the cost-effectiveness of omitting the sentinel node biopsy for clinically T1-2N0 breast cancer patients undergoing breast conserving therapy, a Cost-Effectiveness Analysis (CEA) will be conducted. The CEA will take both a societal and health care perspective and will be expressed as incremental societal costs per Quality Adjusted Life Years (QALY) and healthcare costs per case regional recurrence and case of lymphedema. The CEA will include 474 patients.

The inclusion percentage of the cost-effectiveness study is 66%. At least 474 patients needed to be included for this sub-study. Since the quality of life research is of great importance for estimating QALYs, the quality of life- questionnaire is extended until the inclusion of the CEA –study is completed. With an inclusion rate of 66%, 1056 patients should be included (explanation: 1056 needed for the study, now 951 already included).

**Data-collection and analysis**

The cost-analysis will be performed according to the micro-costing method, whereby a detailed and complete analysis of the resource use and costs of each patient up to 3 years after inclusion will be performed. Costs will be calculated by multiplying resource use with the prices per unit of resource.

Volumes of use will be collected by means of the electronic Case Report Forms (eCRF) as shown in chapter 10 ”ADMINISTRATIVE ASPECTS AND PUBLICATION”, section a “handling and storage of data’ on page 35’ Resource use outside the hospital such as general practitioner costs and costs due to effect on work participation/productivity losses will be collected by means of a standardized retrospective cost questionnaire with a recall period of 3 months, which will be administered on the same

moments as the quality of life questionnaires. Guideline prices will be used [64, 65]. Otherwise, integral cost prices will be obtained from the Maastricht University Medical Centre, or cost-price calculations will be performed. Costs and effects will be discounted according to Dutch pharmaco-economic guidelines. Standard sensitivity analyses and bootstrap analysis will be performed to investigate the uncertainty surrounding the cost-effectiveness ratios [66]. Based on the bootstrap results, cost-effectiveness acceptability curves will be constructed, showing for a wide range of cost-effectiveness threshold values, the probability that omission of the SLNB is cost-effective. Additionally, a decision analytical model will be developed in which the costs and benefits will extend to a lifetime period. The lifetime course of the cohort will be modelled with a Markov model. The model will contain health states like “disease-free”, “regional recurrence”, “lymphedema”, “death from cancer”, “death from other causes” and possible combinations.

***g. Budget impact analysis***

A budget-impact analysis (BIA) will be performed according to the ISPOR guidelines [67]. The BIA addresses the financial stream of consequences related to omitting of the SLNB. The budget impact will depend on the savings due to omission of the SLNB and its consequences (as calculated in the cost- analysis), as well as the uptake of this new strategy by surgical oncologists. Analyses will be focused from the perspective of the national government and the health care insurers over a 5-year time horizon. In addition, the budget impact will be calculated from a broad societal perspective and from the perspective of the “budgettair kader zorg (BKZ)”. Different scenarios will be the scenarios in which SLNB is omitted in 25%, 50%, 75% and 100% of the Dutch hospitals. Furthermore, scenarios will be modelled in which the timeline of de-implementation of SLNB in 100% of the hospitals is varied between direct implementation to implementation in 5 years The BIA will be performed alongside the cost effectiveness analysis.

***h. Withdrawal of individual subjects***

Patients can leave the study at any time for any reason if they wish to do so without any consequences,

and without having to specify the reason for withdrawal. The investigator can decide to withdraw a subject from the study for urgent medical reasons. Withdrawal of patients during the follow-up period will be counted to the 10% of lost to follow-up.

***i. Premature termination of the study***

After premature termination of the study, the investigators must contact all participating subjects within

4 weeks. No new patients are included in the trial. Follow-up of participating subjects will continue, following the study protocol. In case of premature termination of the study due to a higher regional recurrence rate than expected as determined by the DSMB, this will not have a direct consequence for the treatment or follow-up of every study patient that has been randomized for study arm B. So in these patients, delayed axillary treatment is not standardly performed, but only if nodal metastases become clinically apparent.

***j. Final statistical analysis***

Primary and secondary endpoints will be analysed per protocol and in the intention to treat population

after 5 and 10 years of follow-up. Primarily, uncorrected chi-squared statistics will be used to evaluate the null hypothesis, as described in chapter 6, section d ‘Sample size calculation’ on page 19. The chi- square test will be based on the Kaplan-Meier estimator, in case of censored data. Additionally, cox proportional hazards models and Kaplan Meier estimates will be used to analyse the outcome of both groups and to assess the univariable and multivariable association between prognostic variables, treatment and events, using the stratification factors. All statistical tests are 1-sided and a P value of 0.05 or less is considered statistically significant.

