**Secondary study endpoints**

⮚ *Regional recurrence free survival*

Regional recurrence free survival is defined as the time interval between the date of randomization and the date of first suspicion of regional recurrence or date of death, whichever comes first, measured in days. Patients who did not experience regional recurrence and are still alive are censored at the date of last follow-up.

⮚ *Delayed axillary treatment*

This is defined as the number of patients in in whom delayed axillary treatment (any kind) >6 months

after randomization was performed in case of regional recurrence, with the time interval between the date of randomization and the date of the delayed ALND, measured in days.

⮚ *Distant-disease free survival*

Distant-disease free survival is defined as the time interval between the date of randomization and the

date of first suspicion of distant recurrence or death, whichever comes first, measured in days. Patients in whom a distant recurrence was not observed and are still alive are censored at the date of last follow- up.

Included are: distant recurrence (distant metastasis), death from breast cancer and its treatment, death from second primary invasive (nonbreast) cancer death from unknown cause. N.B.: lymph node recurrence in cervical lymph nodes or in contralateral internal mammary lymph nodes or in the contralateral axilla is coded as distant metastasis.

Excluded are: ipsilateral breast tumour recurrence, regional invasive recurrence, contralateral breast cancer, and all in situ carcinomas, as these events are potentially nonlethal.

⮚ *Overall survival*

Overall survival is defined as the time interval between the date of randomization until death from any

cause. Patients who are still alive are censored at the date of last follow up.

Included are: death from breast cancer, death from nonbreast invasive cancer cause, death from unknown cause.

⮚ *Local recurrence rate*

Local recurrence is defined as any pathologically proven invasive in-breast recurrence in the ipsilateral

breast after breast surgery. The local recurrence free interval is defined as the time interval between the date of randomization and the date of first clinical suspicion of local recurrence, measured in days.

⮚ *Other-regional recurrence rate*

Other-regional recurrence is defined as pathologically proven recurrence in the region of the ipsilateral

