internal mammary lymph node chain (lymph nodes in the intercostal spaces along the edge of the sternum in the endothoracic fascia). Other-regional recurrence free interval is defined as the time interval between the date of randomization and the date of first clinical suspicion of other regional recurrence, measured in days.

⮚ *Contralateral breast cancer rate*

The occurrence of (pathologically proven) contralateral invasive breast cancer will be registered. Contralateral breast cancer free interval is defined as the time interval between the date of randomization and the date of first clinical suspicion of contralateral breast cancer, measured in days.

⮚ *Diagnosis of recurrence outside the axillary region*

One or more of the following must be positive for the diagnosis of tumour recurrence to be accepted:
I. Histology or cytology

II. Autopsy examination

Diagnosis based on radiological findings can be considered if I or II is not possible/available (these
cases will be presented to the Data Safety Monitoring Board (DSMB) for an independent review).

⮚ *Percentage difference in the administration of (neo)adjuvant systemic therapy*

This is defined as the percentage difference in the administration of (neo)adjuvant systemic therapy

between both study arms.

- *Quality of Life*

Quality of Life will be assessed using validated questionnaires, as shown in chapter 7 ‘METHODS’, section e ‘Study procedures - axillary morbidity rate and quality of life’ on page 27.

⮚ *Axillary morbidity rate*

The axillary morbidity rate will be assessed using validated questionnaires, as shown in chapter 7

‘METHODS’, section e ‘Study procedures - axillary morbidity rate and quality of life’ on page 27.
⮚ *Cost-effectiveness*

The cost-effectiveness will be assessed by using patient questionnaires, as shown in chapter 7 ‘METHODS’, section f ‘Cost-effectiveness analysis’ on page 28 and electronic Case Report Forms (eCRF) as shown in chapter 10 ADMINISTRATIVE ASPECTS AND PUBLICATION on page 34.

1. ***Study procedure – diagnosis and randomization***

*Diagnosis*

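### Kaplan-Meier is the only time-to-event estimator named, yet three secondary intervals leave death out, so their reported rates, mainly at 10 years, would be somewhat too high

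*Protocol*

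**What the plan says.** Section 7.j of the protocol (Final statistical analysis) sets its scope in its first sentence: "Primary and secondary endpoints will be analysed per protocol and in the intention to treat population", "after 5 and 10 years of follow-up". The main method is an uncorrected chi-squared statistic, and of that test the section says that the "square test will be based on the Kaplan-Meier estimator, in case of censored data". It then adds that "cox proportional hazards models and Kaplan Meier estimates will be used to analyse the outcome of both groups". Neither competing risks nor cumulative incidence appears anywhere in the protocol.

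Section 7.a defines the endpoints. Regional recurrence free survival, distant-disease free survival and overall survival all count death and censor women who are alive at last follow-up. Three other endpoints are headed as rates and carry an interval that ends only at the event itself:

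- Local recurrence: "The local recurrence free interval is defined as the time interval between the date of randomization and the date of first clinical suspicion" of that event.
- Other-regional recurrence: "Other-regional recurrence free interval is defined as the time interval between the date of randomization and the date of first clinical suspicion" of that event.
- Contralateral cancer: "Contralateral breast cancer free interval is defined as the time interval between the date of randomization and" the first clinical suspicion of it.

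For these three, section 7.a gives no censoring rule and does not say what happens to a woman who dies first.

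**The concern.** Kaplan-Meier treats a censored woman as still able to have the event later. That is reasonable for a woman lost to follow-up but not for one who has died. When the endpoint leaves death out and deaths are censored, one minus Kaplan-Meier estimates the risk in a setting without death, not the share of randomised women who have a local, internal mammary or contralateral event.

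Deaths will occur here. Section 6.b sets no upper age limit, women over 75 form a randomisation stratum (section 5.a), and follow-up lasts 10 years. Section 4 makes non-inferiority on local recurrence and contralateral cancer a secondary objective, so readers will use the absolute rates in each arm to weigh the risk of omitting the sentinel node procedure.

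**Working it through.** **The plan's own figure.** The protocol gives no expected rate for the three endpoints. Its sample size in section 6.d reproduces: (1.645 + 0.842)² × (0.96 × 0.04 + 0.99 × 0.01) / (0.05 − 0.03)² ≈ 747 per arm. It does not depend on this point.

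**Inputs.**
- Analysis times of 5 and 10 years: section 7.j.
- Mortality: section 3 cites overall survival of 91.8% and 92.5% in the two arms of the ACOSOG Z0011 trial at a median follow-up of 6.3 years. Those women were sentinel-node positive, so this is only a nearby figure.
- Event rate: assumed, 1 − KM of 5.0% at 10 years.
- Constant hazards: assumed.

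**Formulas.** With event hazard h and death hazard m:
- 1 − KM with deaths censored = 1 − exp(−ht)
- cumulative incidence = h/(h + m) × (1 − exp(−(h + m)t))

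The first exceeds the second whenever m > 0.

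**Hazards.** h = −ln(0.95)/10 = 0.00513 per year. From 91.8% at 6.3 years, m = −ln(0.918)/6.3 = 0.01358 per year, which means 6.6% dead at 5 years and 12.7% at 10 years. A rounder assumption of 7.5% dead at 5 years gives m = 0.01559 and 14.4% dead at 10 years.

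**Results.**

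| Mortality basis | Time | 1 − KM | Cumulative incidence | Overstatement (share of true value) |
|---|---|---|---|---|
| 91.8% survival at 6.3 years | 5 y | 2.53% | 2.45% | 3.4% |
| 91.8% survival at 6.3 years | 10 y | 5.00% | 4.68% | 6.9% |
| 7.5% dead at 5 years | 5 y | 2.53% | 2.44% | 3.9% |
| 7.5% dead at 5 years | 10 y | 5.00% | 4.63% | 7.9% |
| 10% dead at 10 years (assumed) | 10 y | 5.00% | 4.75% | 5% |
| 20% dead at 10 years (assumed) | 10 y | 5.00% | 4.49% | 11% |
| 30% dead at 10 years (assumed) | 10 y | 5.00% | 4.21% | 19% |

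The other cited survival figure, 92.5%, gives slightly less: 3.1% at 5 years and 6.3% at 10 years. The relative overstatement hardly depends on the event rate at these low rates.

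**Difference between arms**, with equal mortality in both:
- 4% vs 1% at 5 years by 1 − KM is 3.0 points. With 5–10% dead at 5 years, cumulative incidence gives 2.9–2.8 points.
- 7% vs 5% at 10 years by 1 − KM is 2.0 points. With 10–30% dead at 10 years, cumulative incidence gives 1.9–1.7 points.

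**The case against.** The strongest reply is that the protocol never says deaths will be censored for these intervals, that Kaplan-Meier is named as an addition to a chi-squared test, and that the handling of competing deaths normally belongs in the statistical analysis plan, which is not shown. This stands in part: the overstatement is conditional on censoring deaths, and the analysis plan may already deal with it. It does not remove the point. Section 7.j covers the secondary endpoints, bases even the chi-squared test on Kaplan-Meier when data are censored, and refers none of this to another document; section 8.c refers only the interim rules to the analysis plan. Following the text as written, an analyst would have no option but to censor deaths.

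A second reply is that the effect is small and errs on the safe side. That is largely right. Where the study arm is worse, inflating the difference works against declaring non-inferiority, and section 6.d sets a margin only for regional recurrence free survival. Cox models that censor deaths remain valid as comparisons of cause-specific hazards.

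A reader might also infer more than the text supports:
- **That Kaplan-Meier is planned for every outcome.** Section 7.j names no individual endpoint in that sentence and cannot mean quality of life, costs or the percentage given systemic therapy.
- **That delayed axillary treatment has the same fault.** It is defined first as a number of patients, with a time attached. No Kaplan-Meier rate is stated for it.
- **That rates in women over 75 would be overstated by 38–52%.** That needs an assumed 10-year mortality of 50–60% in that stratum. The protocol gives no such figure and plans no separate rates for it.

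**Conclusion.** The point holds in limited form. The estimator named in 7.j does not suit the local recurrence, other-regional recurrence and contralateral cancer intervals as section 7.a defines them. With deaths censored, the reported proportions would be too high by about 3–4% of their value at 5 years and about 7–8% at 10 years near the protocol's own cited mortality. In absolute terms that is about 0.1 and 0.3–0.4 points for an event with 1 − KM of 5% at 10 years. An assumed 10-year mortality of 30% raises the 10-year figure to about 19%, or 0.8 points. These sizes rest on constant hazards, an assumed event rate and mortality borrowed from a different population.

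The damage is to absolute rates, chiefly at 10 years. The documents do not support reading this as a threat to the non-inferiority conclusions: with similar mortality in both arms the difference moves by 0.1–0.3 points in the examples above. The sample size is unaffected.

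**What to change.** Add to section 7.j that, for local recurrence, other-regional recurrence and contralateral breast cancer, cumulative incidence will be estimated with death as a competing event (Aalen-Johansen), and that the difference between arms will be reported at 5 and 10 years with its confidence interval. Apply the same rule to any time-based rate of delayed axillary treatment, and to regional recurrence whenever death is not counted; the main endpoint in section 7.a is defined without death, whereas the sample size in 6.d is stated for regional recurrence free survival, which includes it.

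Keep the Cox models and label their results as cause-specific hazard ratios. Keep Kaplan-Meier for regional recurrence free survival, distant-disease free survival and overall survival. If the analysis plan already says this, aligning 7.j with it is enough.

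The cost is a few lines of text and standard software. No patient procedure, data item or sample size changes; the reported rates become slightly lower.
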